##### Subgroup analyses

Potential effects of the following pre-specified subgroups on the endpoint UACR levels will be tested using the model described for the main analysis in “Main analysis model” section extended to include the subgroup and subgroup by treatment interactions: (1) gender, (2) baseline age group (younger than the median and equal to or older than the median), (3) duration of diabetes mellitus at baseline (shorter than the median and equal to or longer than the median duration), (4) body mass index (BMI) at baseline (lower than the median and equal to or higher than the median value), and (5) glycated haemoglobin (HbA1c) level at baseline (lower than the median and equal to or higher than the median value). Likelihood ratio tests will be used to test for interactions and the results will be presented on forest plots with the interactions results alongside. The results will also be presented as outlined in Table 4.

**Table 4 Tab4:** Subgroup analyses in the intention-to-treat group, to be presented as forest plots

Subgroup	Number (%)		Estimated mean difference^a^	95% Confidence Interval	*P* value
	Intervention (GKT137831) group (*n* = xxx)	Placebo group (*n* = xxx)			
Sex					
Male					
Female					
Age					
< median					
≥ median					
Diabetes mellitus duration					
< median					
≥ median					
BMI					
< median					
≥ median					
HbA1c					
< median					
≥ median					

*BMI* body mass index, *HbA1c* glycated haemoglobin

^a^ In the intervention group compared to placebo

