### Sample size

Up to 284 participants in total are expected to be screened (anticipated screen fail rate up to 50%) with 142 participants each randomised to the treatment and placebo groups, to achieve 120 participants reaching the end of the treatment period in total (60 per treatment group). Sect. 2.5 of the protocol [2] provides details of the sample size calculations. In brief, the assumptions of the sample size calculations were the following: mean UACR of 13.56 mg/mmol in the control arm, difference between UACR means in the treatment arm of 3.56 mg/mmol/L (26% reduction in mean UACR in the treatment arm), equal standard deviations of 7.5 mg/mmol in the two arms, and within-subject correlation of 0.3. Using mixed model analysis of covariance with log-transformed UACR as the outcome, several scenarios were examined: 60 participants per treatment arm are required to achieve power > 90% with an alpha level of 0.05 and two-sided hypothesis testing, and 40 participants per treatment arm are required to achieve power > 90% with an alpha level of 0.05 and one-sided hypothesis testing.

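### Four of the five subgroup interactions are tested on median splits of continuous variables, which loses power if effect modification is gradual (low severity)

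*SAP article*

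**What the plan says.** The Subgroup analyses section takes the main analysis model for log endpoint UACR, "extended to include the subgroup and subgroup by treatment interactions". Gender is a natural category. The other four factors are defined by the median:

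- age at baseline: "younger than the median and equal to or older than the median"
- "duration of diabetes mellitus at baseline (shorter than the median and equal to or longer than the median duration"
- "body mass index (BMI) at baseline (lower than the median and equal to or higher than the median value"
- "glycated haemoglobin (HbA1c) level at baseline (lower than the median and equal to or higher than the median value"

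The section continues: "Likelihood ratio tests will be used to test for interactions and the results will be presented on forest plots". Table 4 has one row below the median and one row at or above it for each of the four. The section gives no numeric cut-points, no reason for choosing the median and no interaction analysis on the continuous scale.

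Elsewhere the same variables are handled as continuous. Table 2 summarises age, BMI and diabetes duration by mean and SD, and HbA1c by median and quartiles.

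**The concern.** A display needs groups; a test does not. Here the binary groups define the tested term. Two people just either side of the median are treated as different, while two people far apart on the same side are treated as alike. If the treatment effect drifts with age, duration, BMI or HbA1c, the information within each half is not used.

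Interpretation suffers a little too. The cut-points are whatever the sample medians turn out to be, so a finding such as a larger effect below the median refers to a value unknown until the data are in. The Additional analyses section repeats the sections from the main model to the sensitivity analyses in the modified ITT and per-protocol sets, without saying whether the ITT medians carry over.

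At stake is the chance of seeing a real effect modifier in a trial planned "to achieve 120 participants reaching the end of the treatment period in total (60 per treatment group". Interaction tests at that size are weak to begin with.

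**Working it through.** **The plan's own figure.** The SAP states power only for the primary comparison: above 90% with 60 per arm two-sided, and with 40 per arm one-sided. Its inputs (Sample size) are means 13.56 and 13.56 − 3.56 = 10.00, SD 7.5 in each arm and correlation 0.3. Reading these as lognormal moments:

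- log SDs: √ln(1 + (7.5/13.56)²) = 0.517 and √ln(1 + (7.5/10)²) = 0.668; pooled 0.597
- difference in log means: 0.394
- SD after baseline adjustment: 0.597 × √(1 − 0.3²) = 0.570
- standard error at 60 per arm: 0.570 × √(2/60) = 0.104, so the expected z is 0.394/0.104 = 3.79
- power: Φ(3.79 − 1.96) = 96.6%; for 40 per arm one-sided, 92.6%

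The stated power is reproduced on this reading. Others fall short: analysis of covariance on the raw scale gives 77.8% and 71.9%. There is no subgroup power in the SAP to reproduce.

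**Information kept by a median split.** When the true interaction is linear in the modifier X, the efficiency of the binary test relative to the linear test is the squared correlation between X and the indicator B of being at or above the median. For standard normal X, cov(X, B) = 1/√(2π) = 0.399 and SD(B) = 0.5. The correlation is 0.399/0.5 = 0.798, and its square is 2/π = 0.637.

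**Power after the split** (two-sided 5%) is Φ((1.96 + z) × √efficiency − 1.96), where z is the normal quantile of the power on the continuous scale. For a normal modifier:

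- 90%: Φ(3.242 × 0.798 − 1.96) = 73%
- 80%: Φ(2.802 × 0.798 − 1.96) = 61%
- 60%: Φ(2.213 × 0.798 − 1.96) = 42%
- 50%: Φ(1.960 × 0.798 − 1.96) = 35%

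**Range over assumed shapes.** The SAP gives no distributions, so these are illustrations. The last two columns are 120 × efficiency and the same power formula.

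| Modifier | Efficiency | Loss | 120 completers act like | 80% power becomes |
|---|---|---|---|---|
| Uniform | 0.750 | 25% | 90 | 68% |
| Normal | 0.637 | 36% | 76 | 61% |
| Lognormal, log-SD 0.3 | 0.590 | 41% | 71 | 58% |
| Lognormal, log-SD 0.5 | 0.517 | 48% | 62 | 52% |
| Exponential | 0.479 | 52% | 57 | 49% |

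**Simulation check.** Likelihood ratio tests with N = 120, 1:1 allocation, a normal modifier, baseline correlation 0.3, no centre effect and 4,000 replicates:

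| True interaction | Linear term | Median split |
|---|---|---|
| Linear | 80.3% | 60.6% |
| Step at the median | 62.3% | 81.7% |
| None (type I error) | 6.2% | 6.1% |

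**On this trial's scale.** Take the expected z of 3.79 from above. Each half holds 30 per arm, so the difference between the two half-sample effects has twice the standard error of the main effect. With a normal modifier and gradual change, the continuous test has z larger by 1/0.798.

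- Halves differ by the whole planned effect: split z = 3.79/2 = 1.895, power 47%; continuous z = 2.375, power 66%.
- Halves differ by half of it: split z = 0.947, power 16%; continuous z = 1.187, power 22%.

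**The case against.** The strongest reply is that the split is a reasonable, pre-specified choice. It gives groups of about equal size, it does not assume that the effect changes linearly, its p value tests the contrast shown beside it in the forest plot, and it wins if the effect steps at the median (81.7% against 62.3%). All of this stands. A reader might infer that the split brings no benefit, or that nothing is lost by dropping it from the test; neither is so.

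A second reply is that a fixed loss of a third cannot be read from the SAP. That also stands. The figure needs a normal modifier and a linear interaction, and moves between about 25% and 52% over the shapes tried. Similarly, the fall from 80% to 61% is not a property of this trial, because the SAP states no interaction effect. For a modest interaction both tests are weak (16% against 22%).

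A third is that letting residual plots decide on non-linear terms, as the section on alternative methods allows for the main model, would loosen a test that is now fully fixed. This is right, and the fix has to avoid it.

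What the objections do not answer is that display and test can be separated. The balanced groups and the forest plot survive a continuous test. The step advantage depends on a threshold at or near this sample's median, and the SAP gives no reason to expect one.

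**Conclusion.** The point holds as a low-severity improvement. Four of the five interaction tests rest on median splits, and under gradual effect modification they lose power: about 36% of the information for a normal modifier with a linear interaction, roughly 25% to 52% over the other assumed shapes, and 80% power down to about 61% in the normal case.

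A reader might go further and conclude that the subgroup tests are invalid or that the trial's main conclusion is weakened. The document does not support that. Type I error was the same for both tests in simulation, at about 6%. The variables, split rule, model and test are all specified beforehand, and the primary analysis does not use the splits. The weakness is one of efficiency and interpretability, and it turns on the assumption that effects change gradually.

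**What to change.** In Subgroup analyses, state that for age, diabetes duration, BMI and HbA1c the likelihood ratio test compares the main model plus the continuous modifier with the same model plus a treatment-by-modifier term. Fix the form now, for example linear in the modifier, and say that it will not be changed after residual plots are seen. Keep the median-group estimates in Table 4 and the forest plot for display. Add a footnote that the interaction p value comes from the continuous model. Gender stays as it is.

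The cost is a short addition to the text and a footnote, with no new data. There are two real downsides: the test then relies on the chosen form, and its p value no longer corresponds exactly to the two estimates displayed beside it.

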##### Missing data methods

An investigation of the patterns of missing data will first be carried out. A summary of which variables contain missing values, proportion of missing values in each variable, and patterns and predictors of missingness will be provided. This summary will then be used to decide on the most appropriate method to handle missing data. If the missing values only arise in the dependent variable, no imputation will be carried out, as the main analysis model, which is a linear mixed effects model, is robust against the missing-at-random (MAR) mechanism. However, if the missing values are present in the covariates, following the trial protocol, if suitable [10], missing values will be handled using multiple imputation [11] considering both bias and precision [12]. The following steps will be undertaken: the missing data in the analysis set will first be assessed by calculating the proportion of missing values, investigating the patterns of missingness in the variables, and identifying predictors of missingness. Based on this, a suitable imputation model that typically consists of all the variables in the analysis model and additional auxiliary variables (i.e., the variables that correlate with the variable with missing values and/or are predictors of missingness) [13] will be used to generate 50 completed datasets with imputed values using a fully conditional specification [14]. If missing values are present in the composite measures (e.g., endpoint UACR and baseline UACR, which are overall measures based on multiple log-transformed UACRs) due to item-level missingness, multiple imputation will be carried out at the item level [15]. The analysis model will then be used in each completed dataset and the results will be combined using Rubin’s rules [16].

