#### Main analysis set (ITT analysis set)

The ITT analysis set is the main analysis set that will be used for evaluating the primary hypothesis, and it consists of all randomised participants with each participant retaining their treatment group as originally allocated by the randomisation procedure.

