#### Primary outcome measure

The primary outcome measure of the trial is the urinary albumin excretion level measured by the urine albumin–creatinine ratio (UACR) in milligrams per millimole at the end of the treatment (endpoint UACR), and is defined as the geometric mean of four UACR values, which consists of the two consecutive, daily, first void UACR values at 46 weeks of treatment and the two consecutive, daily, first void UACR values at 48 weeks of treatment. Baseline UACR is defined as the geometric mean of four UACR values, which consists of the two consecutive, daily, first void UACR values at 2 weeks before randomisation and the two consecutive, daily, first void UACR values at randomisation. In the statistical analyses, endpoint UACR will be adjusted for baseline UACR (see “Primary hypothesis” section).

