##### Midpoint urine albumin–creatinine ratio

The urinary albumin excretion level at the midpoint of the treatment period measured by the urine albumin–creatinine ratio (midpoint UACR), defined as the geometric mean of the two consecutive, daily, first void UACR values taken at the midpoint of treatment at 24 weeks of treatment.

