### Analysis methods

#### Primary analyses

##### Main analysis model

The main analysis will be based on the ITT analysis set. The analysis model will be a linear mixed effects model with endpoint UACR (log-transformed) as the outcome, a categorical variable indicating the allocated grouping structure (intervention versus placebo) as the exposure, and a random effect term to account for the study centre variability. The model will incorporate other covariates as discussed in “Covariate adjustment” section. The results from this analysis will be summarised in Table 3.

**Table 3 Tab3:** Primary and secondary results of the GKT137831 trial

Outcome		Analysis	Mean (standard deviation)		Estimated mean difference^a^	95% Confidence Interval	*P* value
			Intervention (GKT137831) group (n = xxx)	Placebo group (*n* = xxx)			
Primary	Endpoint UACR	Intention to treat (ITT)					
		modified ITT					
		Per protocol (PP)					
Secondary	Midpoint UACR	Intention to treat (ITT)					
		modified ITT					
		Per protocol (PP)					
	Endpoint eGFR	Intention to treat (ITT)					
		modified ITT					
		Per protocol (PP)					
	Midpoint eGFR	Intention to treat (ITT)					
		modified ITT					
		Per protocol (PP)					

*UACR*  urine albumin: creatinine ratio, *eGFR* estimated glomerular filtration rate

^a^ In the intervention group compared to placebo

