##### Sensitivity analyses

The results obtained by using a mixed effects model of the (log-transformed) endpoint UACR with the allocated grouping structure as the exposure, a random effect term to account for the study centre variability, only incorporating (log-transformed) baseline UACR as a covariate without additional baseline covariates will also be made available. In addition, the sensitivity of the results to the decisions made in constructing the imputation model, will be investigated using visualisations of the distributions of imputed and observed values, standard regression diagnostics [17], and comparisons with complete case analysis. The results will be presented as outlined in Fig. 2.

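### When only the endpoint UACR is missing, the plan does not impute it and cites mixed-model robustness under MAR, but this model then gives a complete-case analysis that ignores the week-24 UACR

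*SAP article*

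**What the plan says.** The SAP article's *Missing data methods* section first says that patterns of missingness will be examined and used to choose a method. It then fixes three rules.

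- Outcome only: "If the missing values only arise in the dependent variable, no imputation will be carried out". The reason given is "as the main analysis model, which is a linear mixed effects model, is robust against the missing-at-random (MAR) mechanism".
- Covariates missing: multiple imputation if suitable, by fully conditional specification with 50 datasets. The imputation model typically holds all analysis variables, plus auxiliary variables that correlate with the incomplete variable or predict missingness.
- Composite measures with missing items: multiple imputation at item level. Endpoint UACR is named as an example.

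*Main analysis model* defines the model: "The analysis model will be a linear mixed effects model with endpoint UACR (log-transformed) as the outcome", with arm as exposure and "a random effect term to account for the study centre variability". *Covariate adjustment* adds log baseline UACR and any imbalanced baseline variables. Under *Primary outcome measure* the endpoint is a single number per participant: it "is defined as the geometric mean of four UACR values, which consists of the two consecutive, daily, first void UACR values at 46 weeks" and two more at 48 weeks. Week-24 UACR is a separate secondary outcome, "defined as the geometric mean of the two consecutive, daily, first void UACR values taken at the midpoint of treatment".

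Of the main analysis set the SAP says "it consists of all randomised participants with each participant retaining their treatment group as originally allocated". *Sensitivity analyses* lists "comparisons with complete case analysis" as one check on the imputation model.

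**The concern.** The protection that a mixed model usually gives under MAR comes from a participant's other outcome measurements staying in the likelihood. A participant who drops out still contributes earlier visits, and these carry information about the missing one. This model has no visit term, no participant effect and no earlier UACR among its outcomes. Its only random effect is for centre, which cannot stand in for a participant's own course.

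At stake is the primary estimate. Participants without an endpoint UACR belong to the intention-to-treat set by definition but would not inform the comparison, and the measurement most likely to help, week-24 UACR, would be left out.

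The rules also do not fit together. If all four week-46/48 values are missing, the outcome-only rule says not to impute, while the composite rule can be read as saying impute. If any baseline covariate is missing, the imputation model includes the endpoint, so dropouts would normally be filled in as well. Whether they count could then turn on an unrelated gap in a baseline variable.

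**Working it through.** **1. The plan's own figures.** *Sample size* gives control mean 13.56, difference 3.56 (so 10.00 in the treatment arm), SD 7.5 and within-subject correlation 0.3. Lognormal moments give log SDs √ln(1+(7.5/13.56)²) = 0.517 and √ln(1+(7.5/10)²) = 0.668, pooled 0.597, and a log-mean difference of 0.394. Power is then 95.1% at 60 per arm two-sided and 90.4% at 40 per arm one-sided, which matches the stated figures above 90%. The sample size is not in dispute. These inputs only set the scale below, where the log effect is taken as ln(10.00/13.56) = −0.3045.

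**2. What a participant without an endpoint contributes.** The likelihood term is the density of y given arm, baseline and centre effect. Integrated over an unobserved y it equals 1, so the participant drops out. Check: in one simulated trial with 142 randomised and 125 outcomes observed, the arm effect was −0.2979 with all rows entered and −0.2979 with complete cases only.

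**3. The condition for validity.** The fit is valid if P(observed | y, arm, centre, baseline) does not depend on y. If missingness depends on week-24 UACR, which correlates with y beyond baseline, the data are MAR given week 24 but this condition fails.

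**4. Bias when the true effect is −0.3045.** Assumptions: 15.5% missing, log SD 0.597, correlation 0.3 of baseline with later values, logistic missingness with slope 1 per SD, 400,000 participants per scenario. The columns are the assumed correlation of week 24 with the endpoint. Positive values shrink the effect; percentages are of 0.3045.

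| Missingness depends on | 0.3 | 0.6 | 0.8 |
|---|---|---|---|
| Baseline only | 0.0010 | −0.0007 | −0.0002 |
| Week 24 with drug effect removed, both arms | −0.0007 | −0.0010 | 0.0018 |
| Week-24 level, same rule both arms | 0.0082 (2.7%) | 0.0156 (5.1%) | 0.0197 (6.5%) |
| High week 24, placebo only | 0.0211 (6.9%) | 0.0486 (16.0%) | 0.0630 (20.7%) |
| High in placebo, low in active | 0.0360 (11.8%) | 0.0866 (28.4%) | 0.1146 (37.7%) |

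Imputing from arm, baseline and week-24 UACR (with arm interactions) kept bias within about 0.003 throughout.

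**5. Type I error.** Take log SD 0.52, correlation 0.3 and 60 analysed per arm. SE = 0.52 × √(1−0.3²) × √(2/60) = 0.0906. For a bias b in the drug's favour, the error is 1 − Φ(1.645 − b/SE).

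- b = 0.025: 1 − Φ(1.645 − 0.276) = 8.6%. With the sign reversed, 1 − Φ(1.645 + 0.276) = 2.7%.
- b = 0.05: 1 − Φ(1.645 − 0.552) = 13.7%. With the sign reversed, 1.4%.

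Simulation under the null, with about 16% loss and a week-24/endpoint correlation of 0.3 to 0.7, gave about 7% to 26% for mechanisms favouring the drug, 0.5% to 3.5% when reversed, and about 5% when both arms shared one mechanism.

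**The case against.** Several parts of the defence stand.

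- Repeated outcomes are not the only route to validity under MAR. With only the outcome missing, the model is valid if missingness depends on variables it contains. A reader might infer that the MAR statement is false outright; the fair statement is that it claims more than this model delivers.
- The problem sits in one branch: covariates complete, endpoint wholly missing. A partly observed endpoint is imputed at item level, and week-24 UACR would qualify there as an auxiliary variable. The two rules can be read as a general rule with an exception, but the text does not say so.
- A reader might infer that everyone who worsens or stops treatment leaves the comparison. *Withdrawals/follow up* provides for people who stop the intervention but stay in follow-up; they can still give week-46/48 samples and keep their allocated arm.
- A reader might take 15.5% as the expected share of missing endpoints. It is 1 − 120/142, a non-completion figure, and it reads 142 as the total randomised (284 screened, half failing) although the text says 142 in each group.
- Exclusions are not hidden: the flow diagram described under *Recruitment* reports them with reasons. The complete-case comparison is attached to the imputation model, so where nothing is imputed it has nothing to compare rather than being a false check.

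What the defence does not answer is that the no-imputation rule shuts out the very auxiliary variables that the same section calls predictors of missingness.

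**Conclusion.** The point holds for participants whose endpoint UACR is wholly missing when covariates are complete. In that branch the primary analysis is complete-case, it rests on a narrower condition than the MAR cited, and it discards week-24 UACR. The section also leaves open which rule applies when all four items are missing, and gives no reason why dropouts should be imputed only if some covariate happens to be missing.

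The size is illustrative. The SAP gives no dropout data and does not show that week-24 UACR predicts dropout; mechanisms and correlations are assumed. It is tempting to conclude that the false-positive rate is inflated. The document does not support that, because the sign is unknown: arm-specific dependence on week 24 can push the one-sided 5% error above 10% or down to about 0.5%. It stays near 5% if missingness depends on baseline only, or under the null if both arms share one mechanism. This should be fixed before unblinding, but the primary analysis is not shown to be biased.

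**What to change.** Delete the no-imputation rule and its MAR justification. State instead that, for all randomised participants whose data may be used, missing log UACR items at weeks 46 and 48 are multiply imputed, including when all four are missing. Use the plan's existing fully conditional specification with 50 datasets, with arm, baseline UACR and week-24 UACR in the imputation model alongside the other analysis variables. Keep complete-case as the sensitivity analysis already listed; it then has something to be compared with.

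A longitudinal mixed model that includes week 24, with participant-level correlation, is an acceptable alternative but is not required. A delta-adjusted analysis would be a further preference, not part of this correction.

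The cost is a few sentences and a little programming; no new data are needed. The downside is reliance on the imputation model, and little is gained for participants who leave before week 24.
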